### Description of the intervention

The intervention is targeted at older home care clients who are not able to participate in other activities because of their poor health or functional ability. The day activity service is a complex intervention which means that it has multiple aims and there is variation in how it is carried out in different settings. The principle aim of the day activity service is to support the older home care clients’ ability to live in their own homes by promoting their health and wellbeing, maintaining their physical, psychological, and social functional ability and by enhancing social inclusion. More specifically, the intervention has aims to; maintain memory, promote social interaction, provide peer support, and reduce loneliness and sense of insecurity.

The day activity service is an additional service to the regular home care services and takes place in local day activity centres or other places once a week. It is a group-based intervention, and the duration of one meeting is from 2 to 6 hours. The intervention includes rehabilitative and preventive activities such as physical exercising, outdoor activities, thematic discussions, activating memory, listening to music, having lunch and coffee together with group participants. The day activity service is tutored by practical nurses or home helpers. In the study sites, there are day activity groups of 2 hours, 3 hours, 4 hours, and 6 hours. There is also variation in the content and activities of the intervention. A payment per meeting is between 5 to 23 euros depending on the duration of the service. Transport is arranged if necessary, paying for a local bus ticket.

Home care clients need to apply for the service and get a service decision on it to take part in the day activity service weekly. The criteria for the decision are i) not able to participate in other activities produced by municipalities, private sector or third sector, and ii) is capable of attending group activities. Severe memory disorder can prevent participation, for example.

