### Quasi-experimental trial

#### Participants, selection criteria and recruitment

The target sample size for the intervention study is 200 participants (100 IG + 100 CG) based on previous research with similar study designs (e.g., [19]) and directional sample size calculations. We accepted an alpha risk of 0.05% and a power of 80% at an effect size of 0.5. A theoretical sample of 64 participants in the IG and 64 participants in the CG will be needed. Finally, we assumed that potential attrition rate may be 20–30% due to the functional decline of the participants.

The IG is composed of home care clients aged 65 years or older who are new participants in the day activity service. All new participants of the day activity service are eligible for the IG. The participants are recruited with the help of personnel who are responsible for the official decisions of the day activity service. Personnel or researchers will call older people in receipt of service decisions to access the day activity service and invite them to participate in the study. Researchers will receive the contact details of the day activity service participants from the personnel. Information about the study, an informed consent form and the first questionnaire are sent to those home care clients who agree to participate in the study when calling them. IG participants fill the informed consent form and baseline survey before beginning to participate in the day activity service.

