The CG consists of home care clients aged 65 years or older who do not participate in the day activity service, and whose functioning and health are similar to the participants of the IG. Possible reasons for non-participation include being on the waiting list and not knowing about the service. The CG participants are recruited from the sample of home care clients who attend the other part of the research project from May to October 2022 (see [12]). The sample (target *n* = 1700) of home care clients respond to the same survey used as baseline survey in the quasi-experimental trial. The formation of the CG proceeds in three steps. 1) Potential CG participants are chosen based on the questions and measurements of the survey. The primary indicator is the question: Do you participate in group activities or hobby activities? Those who respond “No, but I would like to participate” are selected as potential CG participants at first stage. 2) After that, the potential respondents for the CG are compared with the respondents who have recently started to attend the day activity service. Comparison is conducted using general indicators related to their functioning and health, such as quality of life (Euro-HIS-8) and perceived health. 3) The invitation and follow-up surveys are sent to 130 home care clients whose functioning and health are as similar as possible to those clients attending the day activity service.

The recruitment of IG participants begins in August 2022 and continues until the target sample size is achieved. The estimated recruitment rate is 14 new study participants per month; therefore the recruitment phase may last until March 2023.

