#### Study conduct

At the beginning, the study participants will complete a long questionnaire (baseline survey). The CG participants will fill their baseline survey as part of the overall study (SOLDEX project). After responding to the baseline survey, IG participants will begin to attend the day activity service meetings once a week. The CG participants will receive home care services as usual and other social and health care services if needed. The three-month and six-month follow-up surveys will be gathered from both intervention and control group participants. Three months is considered as a sufficient time for the first follow up due to the intensity of the service and the functional capabilities of the participants. The follow-up questionnaire is a short version of the baseline survey including relevant measurements and questions for examining the effectiveness of day activity service in terms of the outcome measures. If the study participants do not return the follow-up survey, they will be called and encouraged to continue the study if possible. Throughout the study, the study participants are offered assistance in filling in the survey in case of visual impairment, for example. At the time of follow-up surveys, IG participants will also be interviewed with ASCOT-tool (Fig. 1.)

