Information about the intervention group members’ participation in the day activity service is provided by the municipalities after the six-month trial period.

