#### Statistical analysis

First, descriptive analyses will be conducted to indicate similarities and differences between baseline characteristics in the IG and in the CG. The chi-square test is used to compare categorical variables. Continuous variables will be compared using t-test (normal distribution) and Mann-Whitney U test (non-normal distribution).

Intention-to-treat analyses will be performed primarily and for all outcomes. In addition, per-protocol analyses are used in a supplementary sense. Results of the categorical outcomes will be presented through percentages and continuous outcomes through mean scores and standard deviations or medians and quartiles. To evaluate the effectiveness of the intervention, the data will be analysed using suitable methods for correlated panel data such as mixed effect modelling or generalized estimating equations modelling [30]. Methods of multiple imputation will be used if necessary [31]. The challenges of non-randomization will be taken into account using statistical methods, such as propensity score weighting [32], if necessary.

Subgroup analyses will be performed for age, sex, frequency of participation, research area (two areas) and duration of the intervention (2–4 hours/6 hours). In addition, knowledge on tailoring the group activities learned from interviews with professionals (see Process evaluation) will be utilized in the analyses if necessary.

The data will be reported following the CONSORT guidelines [33].

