#### Study conduct

Individual interviews with the intervention participants will be conducted at the end of the six-month trial. The interview will be composed of three parts: 1) Understanding the participant’s functional ability, needs and services utilised (perceptions of their life situation and coping in every-day life, formal services and support in use, informal support, details and reasons of participating the day activity service), 2) General experiences of the day activity service (description of the day activity service, expectations, the most important activities/contents, perceived benefits and disadvantages, essential factors of successful service, barriers to participation, experiences of social inclusion and client-centredness, development ideas), 3) Experiences of the components of the day activity service (social activities, physical activities, other activities, tutors, lunch, information and advice) to explore how the components contribute to the overall intervention.

Focus group interviews with professionals will be conducted after halfway through the trial. Focus group interviews include three main sections: 1) Experiences of delivering the day activity service (aims, contents, duration, and participants of the intervention in different areas, any adaptations or tailoring made during delivery), 2) Factors affecting the implementation (organizational, professional and client-related barriers and facilitators of implementation), 3) Development of the intervention and understandings of how the intervention and its components are intended to work (program theory). The first section will include consideration of how different practices adopt the intervention and any local adaptations made. This knowledge related to tailoring/adaptation will be utilized in statistical analyses of the quasi-experimental trial. For example, by grouping participants based on major differences in tailoring of the day activity group they attend.

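### Frequency of participation is listed as a subgroup variable, but it exists only in the intervention group and is known only after follow-up; session duration is also undefined in the comparison group

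*Protocol article*

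**What the plan says.** The Statistical analysis section of the quasi-experimental trial puts five variables in one list: "Subgroup analyses will be performed for age, sex, frequency of participation, research area (two areas) and duration of the intervention". Duration is split as "duration of the intervention (2–4 hours/6 hours". Nothing separates frequency and duration from the other three or marks them as analyses within the IG.

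Other sections of the article fix what these two variables can be:

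- Participants, selection criteria and recruitment: "The CG consists of home care clients aged 65 years or older who do not participate in the day activity service".
- Study conduct (trial): "The CG participants will receive home care services as usual and other social and health care services if needed". The same section has IG members attending weekly.
- Outcomes and variables, on IG members: "participation in the day activity service is provided by the municipalities after the six-month trial period".
- Description of the intervention: "In the study sites, there are day activity groups of 2 hours, 3 hours, 4 hours, and 6 hours". The fee depends on the length of the meeting.
- Sample-size paragraph: attrition of 20–30% is expected "due to the functional decline of the participants".
- Study conduct (process evaluation): knowledge about tailoring may enter the trial analysis, for example "by grouping participants based on major differences in tailoring of the day activity group they attend".

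Intention-to-treat is primary for all outcomes and per-protocol is supplementary. Propensity score weighting is named, if necessary, to deal with non-randomization.

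**The concern.** A subgroup effect is the IG–CG difference within a level of a characteristic that both groups have at baseline. Frequency of participation fails on both counts. CG members have no value for it, and in the IG it builds up during the same six months in which the outcome develops.

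Any analysis by frequency must therefore compare IG members with each other, or compare a self-selected part of the IG with a CG that has not been selected in the same way. Either can show a difference when the service does nothing, if staying well both keeps people attending and keeps their inclusion and loneliness scores up.

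Duration shares the first problem only. It belongs to the group attended, so it is not an outcome of the participant's health during follow-up. It may still differ by place, participant mix or ability to pay.

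At stake are statements such as that the service works when attended often, or that six-hour groups work. The Implications section says the results should show whether the service needs redesign, and these are findings that a provider would act on.

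**Working it through.** **1. Which variables allow an IG–CG contrast within levels?**

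| Variable | Defined in CG? | Fixed at baseline? | IG–CG contrast within levels |
|---|---|---|---|
| Age, sex | yes | yes | yes |
| Research area | yes | yes | yes |
| Frequency of participation | no | no | no |
| Session duration | no | a feature of the group attended | only if the CG is re-weighted to resemble each stratum |

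Meetings are weekly for all IG members, so variation in frequency is mainly attendance behaviour and not an assigned dose.

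**2. The article's own yardstick.** It gives no figure for the subgroup analyses. Its design figure is 64 per group at effect size 0.5 and 80% power. A two-sample t-test at two-sided 5% gives 63.8, so 64, which reproduces it. The article prints alpha as 0.05%, which would give 152.5; that is a separate matter. The yardstick used here is 0.5 SD.

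**3. Size of a possible selection bias.** The correlations below are assumptions; the article supplies none.

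- The service has no effect, and IG and CG have the same outcome distribution.
- Attendance A, functional decline D and outcome change Y are standardised and jointly normal.
- D correlates −r with A and −r with Y, and is the only link between them. Hence corr(A, Y) = r².
- The IG is split at median attendance. The upper half of a standard normal has mean √(2/π) = 0.798.

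Better-attending half minus whole CG = 0.798 × r².
Better-attending minus worse-attending half = 2 × 0.798 × r² = 1.596 × r².

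| r | r² | Better half − worse half (SD) | Better half − whole CG (SD) |
|---|---|---|---|
| 0.3 | 0.09 | 0.14 | 0.07 |
| 0.4 | 0.16 | 0.26 | 0.13 |
| 0.5 | 0.25 | 0.40 | 0.20 |

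At r = 0.4 the spurious difference is about half the design effect within the IG (0.26/0.5) and about a quarter against the CG (0.13/0.5).

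**4. False-positive rates.** These come from a simulation with no effect, 70 completers per group (100 less 30%), halves of 35, nominal 5% tests and 4,000 runs. The direct attendance–outcome correlation, which is r² above, was set at 0, 0.1 and 0.2.

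| Attendance–outcome correlation | Better v worse half | Better half v whole CG |
|---|---|---|
| 0 | 4% | 5% |
| 0.1 | 10% | 7% |
| 0.2 | 26% | 13% |

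The value 0.1 lies close to r = 0.3 (r² = 0.09), and 0.2 lies between r = 0.4 and r = 0.5.

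**5. Does anything in the article already deal with this?** Propensity weighting balances baseline characteristics between IG and CG. It cannot remove selection that arises from changes in health during follow-up. Intention-to-treat protects the main comparison, but a split by attendance leaves that comparison behind.

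**The case against.** The strongest reply is that this is a condensed article. Interaction tests, adjustment sets and labels usually sit in a full analysis plan, and the authors may intend an ordinary within-IG analysis by attendance. The article nowhere says that frequent attenders will be set against the whole CG. That is fair as far as missing detail goes. It does not cover the classification itself: the article places an IG-only, post-baseline variable in the same list as age and sex.

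Several stronger readings are tempting, and the article does not support them:

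- *Frequent attenders will look better.* The sample-size paragraph ties functional decline to loss from the study, not to missed meetings. The direction is plausible but not documented.
- *The bias against the CG is 0.26 SD at r = 0.4.* That figure compares the two halves of the IG. Against the whole CG it is 0.13.
- *No between-group effect exists for duration.* A contrast of six-hour attenders with a suitably re-weighted CG is a legitimate estimate for that form of the service. It is harder to form, but not impossible.
- *Duration is mixed up with locality.* The article says that groups of four lengths exist in the study sites, not which places offer which. Confounding with place is possible; only the link between fee and duration is stated.
- *Tailoring is a planned subgroup.* It is not in the list. A separate sentence allows its use if necessary, and the process evaluation gives grouping as an example.

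**Conclusion.** The point holds for frequency of participation. It has no value in the CG and is known only after follow-up, so no IG–CG subgroup contrast exists for it. A comparison by attendance may be biased, by about 0.14–0.40 SD between halves of the IG or about 0.07–0.20 SD against the whole CG. Those sizes rest on assumed correlations of 0.3–0.5, on functional decline being the only link, and on a median split. They show what could happen and do not estimate what will.

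For duration the point is weaker: there is no CG counterpart, and confounding with place, participant mix and fee is possible. No size can be put on it from the article.

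A reader might infer that the trial's main result is in doubt. It is not: the primary intention-to-treat conclusion is unaffected. The list should be changed because the subgroup findings could guide redesign of the service.

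**What to change.** - Keep age, sex and research area as between-group subgroups, each tested by a group-by-subgroup interaction.
- Move frequency of participation to an exploratory, IG-only analysis adjusted for baseline ESIS, health and functioning. Label it non-causal, because baseline adjustment cannot remove selection that arises during follow-up.
- Treat duration in the same way, with adjustment for area added. If a contrast with the CG is wanted, re-weight the CG to each duration stratum on baseline covariates and area.
- If participants are grouped by tailoring, treat that as IG-only and exploratory too, and fix the classes before outcome data are seen.

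The cost is wording only; no new data are needed. The downside is that no causal claim of effectiveness by attendance can be made.

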### Economic evaluation

#### Study conduct

The economic evaluation (cost-effectiveness analyses, CEA) is part of the quasi-experimental trial design. Therefore, the study population and selection criteria will be the same as described previously.

#### Costs

The administrative data of social and health care service use and the costs of the intervention will be utilized in examining the cost-effectiveness of the intervention [34]. Costs of the day activity service will be retrieved from the service providers. Costs of health and social services will be calculated based on service use and the unit costs of the services [35].

#### Outcomes

Outcome measures for social inclusion, loneliness and social care related quality of life are the same as described in previous section.

#### Statistical analysis

The cost-effectiveness of the intervention will be analysed in relation to home care without day activity service using the incremental cost-effectiveness ratio (ICER) [36]. The ICER indicates between-group differences in costs and outcomes in 3- and 6-months follow-up periods, and will be calculated as follows:$$\textrm{ICER}=\left({\Delta \textrm{C}}_{\textrm{IG}}-{\Delta \textrm{C}}_{\textrm{CG}}\right)/\left({\Delta \textrm{E}}_{\textrm{IG}}-{\Delta \textrm{E}}_{\textrm{CG}}\right)$$

where

∆C_IG_ = change in mean costs in the intervention group.

∆C_CG_ = change in mean costs in the control group.

∆E_IG_ = change in mean effectiveness in the intervention group.

∆E_CG_ = change in mean effectiveness in the control group.

Bootstrap simulation will be conducted to describe the statistical uncertainty related with the observed ICER. The probability distribution of ICER will be examined graphically by cost-effectiveness planes and cost-effectiveness acceptability curves.

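### The ICER is fixed as an unadjusted difference in group mean changes, although the groups are not randomised and enter at different kinds of time point, so it relies on parallel cost trends that nothing in the plan protects

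*Protocol article*

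**What the plan says.** **The estimator.** Under Economic evaluation, Statistical analysis, the numerator is the "change in mean costs in the intervention group" minus the "change in mean costs in the control group". The denominator has the same form for effectiveness. The formula contains no covariate or weight. The text before it says: "The ICER indicates between-group differences in costs and outcomes in 3- and 6-months follow-up periods". The period from which a change is measured is not defined. Bootstrap simulation, cost-effectiveness planes and acceptability curves are to describe uncertainty. Under Costs: "Costs of health and social services will be calculated based on service use and the unit costs of the services".

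**Adjustment.** In the quasi-experimental trial's own Statistical analysis section: "The challenges of non-randomization will be taken into account using statistical methods", with propensity score weighting as the example and only where needed. Strengths and limitations adds, in general terms, that baseline differences will be considered in analysis.

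**Time origins.** Intervention group: "Home care clients need to apply for the service and get a service decision on it" (Description of the intervention). Personnel or researchers then "call older people in receipt of service decisions to access the day activity service", and the baseline survey is completed after the decision and before attendance starts (Participants, selection criteria and recruitment). Comparison group: its members are "recruited from the sample of home care clients who attend the other part of the research project from May to October 2022", and that survey serves as their baseline. They are chosen on indicators of functioning and health; prior cost and prior service use are not named.

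**The concern.** One group is indexed at a care event and the other at a survey date tied to no care event. A difference in changes removes a stable cost gap between such groups. It does not remove a gap that is opening or closing around the event. Service use may be temporarily high or low before a new decision, or may keep rising with need. Any of these movements would be attributed to the day activity service.

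At stake is the sign of the incremental cost, and with it the conclusion that the Implications section offers to decision makers allocating scarce resources. There is also a consistency problem. If the effectiveness analysis is weighted and the ICER is not, the ICER's denominator will not be the effect that the trial reports.

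**Working it through.** The article gives no cost, cost variance or ICER, so there is no plan figure to reproduce. The check is algebra on the printed formula, then an illustration on assumed costs.

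**1. The formula.** With mean cost per window of equal length before and after entry,

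N = (post_IG - pre_IG) - (post_CG - pre_CG).

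Let τ be the true cost effect and U the usual cost. Compare N with two alternatives: the follow-up difference F = post_IG - post_CG, and F adjusted by regression on pre-entry cost, A = F - ρ(pre_IG - pre_CG). Here ρ is the pre/post correlation, taking equal spread in both windows.

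| Situation in the intervention group only | N | F | A |
|---|---|---|---|
| Parallel trends, equal levels | τ | τ | τ |
| Temporary pre-entry excess P | τ - P | τ | τ - ρP |
| Temporary pre-entry dip of size P | τ + P | τ | τ + ρP |
| Rise in need G, continuing after entry | τ + G | τ + G | τ + G |
| Stable cost difference D | τ | τ + D | τ + (1 - ρ)D |

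No single estimator is right in every row. The printed formula is right only in the first and last, where trends are parallel.

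**2. Illustration.** Assumed, not from the article: lognormal costs, usual cost 100 per window, coefficient of variation 1.0, within-person correlation 0.6 on the log scale, τ = 0. There are 100 per group, as in the target sample. Simulated means:

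| Pre-entry peak | Expected N = -P | Simulated N | F | A |
|---|---|---|---|---|
| -20% (dip) | +20 | 20.0 | 0.3 | 10.8 |
| 0% | 0 | 0.2 | 0.5 | 0.4 |
| 10% | -10 | -10.3 | -0.3 | -5.6 |
| 20% | -20 | -19.9 | -0.2 | -10.7 |
| 30% | -30 | -30.2 | 0.1 | -15.9 |
| 50% | -50 | -49.9 | 0.0 | -26.8 |
| 100% | -100 | -100.0 | 0.1 | -53.5 |

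The simulated N matches the algebra. Regression on immediate pre-entry cost leaves just over half of the shift (10.7/20 = 0.54). This is close to the ρ implied on the cost scale: ln(1 + 1.0²) = ln 2, so ρ = (2^0.6 - 1)/(2 - 1) = 0.52.

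**3. Sign reversal.** With a true added cost of 15, a 20% peak gives 15 - 20 = -5 (simulated -5.5). A 30% peak gives 15 - 30 = -15 (simulated -15.1).

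**4. Bootstrap.** Resampling describes the spread around N, not its distance from τ. With τ = 0, N was negative in 49% of simulated trials without a peak and in 92% with a 20% peak. Planes and acceptability curves built on N would inherit that shift.

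**The case against.** A reader might infer that the plan will show false savings, because entry follows a recognised need. The documents do not support that. They show entry triggered by a decision, not a cost peak. The decision criteria are being unable to join other activities and being capable of attending a group, and neither is a costly event. The sample size paragraph expects functional decline, which fits rising costs at least as well. The direction therefore stays open.

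A reader might also infer that regressing follow-up cost on pre-entry cost settles the matter. It does not: it leaves -ρP under a temporary peak, and under a stable cost difference the change score is the less biased of the two. Because the comparison group is not selected on prior cost, a stable difference is plausible. The difference in changes is a standard quasi-experimental estimator, and this point does not call it wrong in itself.

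Third, the article is condensed. The formula does not forbid weighted means, a full plan may set the cost windows, and the limitations paragraph promises in general terms to consider differences. The reference to 3- and 6-month follow-up periods might even mean follow-up costs only, in which case a pre-entry peak never enters.

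These points limit the claim but do not remove it. The printed estimator uses plain group changes, and the general sentence does not alter it. Under the follow-up-only reading, the word change has no referent and the comparison remains unadjusted between non-randomised groups.

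**Conclusion.** The point holds in a limited form. As printed, both parts of the ICER are unadjusted differences in group mean changes. The groups are not randomised, have different time origins, and are not selected on prior cost. Parallel trends are assumed with no stated check. If change is measured from a pre-entry window, the numerator moves one for one with any temporary pre-entry departure in the intervention group: 10 to 50% of usual cost appears as a saving of 10 to 50%, and a 20% dip as an added cost of 20%. Those percentages are assumptions. The documents give neither size nor direction, so this is an unprotected estimator and not a demonstrated bias. It is still worth changing, because the remedy is cheap and the data are already planned.

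**What to change.** In the economic evaluation's Statistical analysis section:

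- Define the pre-entry and follow-up cost windows for each group.
- Estimate incremental cost and incremental effect as between-group differences using the same propensity weights as the effectiveness analysis. Add to the weights a cost history from a window ending some months before the service decision or survey date, so that usual cost is balanced without conditioning on a possible peak or dip.
- Bootstrap costs and effects jointly by person, re-estimating the weights in each sample.
- Plot monthly pre-baseline costs by group.
- Report as sensitivity analyses the raw change formula, a version omitting the last months before baseline, and follow-up cost adjusted for prior cost. Do not describe the last of these as a full correction.

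The weights do not align the two time origins, and no listed estimator removes a continuing rise in need. The plot is what lets a reader judge whether either matters. The cost is a few sentences, modest programming on the administrative data already planned, and possibly slightly wider intervals from weighting.
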